### Recruitment

2.2

Participants will be recruited from the Department of Neurology at West China Hospital of Sichuan University. Researchers will recruit participants by approaching potentially eligible participants in the neurology ward. Inclusion criteria of participants are (1) newly admitted patients diagnosed as stroke, including ischemic or hemorrhagic strokes for the first time, (2) 60 years old and above, (3) conscious and in stable condition with stable vital signs, whether in the acute, subacute, or chronic phase of stroke, (4) with upper limb dysfunction and Brunnstrom stages I to VI, (5) normal cognitive function without minimal aphasia or hemineglect, (6) normal vision, hearing, and communication, (7) no music-related learning experience and acceptance of music, and (8) participating in this study voluntarily and signing the informed consent form. Exclusion criteria are (1) severe primary diseases of the heart, liver, kidney, and hematopoietic system, (2) a history of mental disease, (3) joint dislocation or skin damage of the upper limb, (4) largest slice diameter of cerebral infarction is greater than 3.0 cm, or the infarction spreads to two brain lobes, or the volume of intracerebral hematoma is greater than 30 mL, (5) uncooperative participants, (6) depression according to the Self-rating Depression Scale. After determining the eligibility of interested patients, the researchers will describe the details of this study to them again, obtain written consent forms, and collect baseline data.

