### Outcomes and measurements

2.6

A research assistant who does not know the randomization scheme will perform the data collection and examinations at baseline (T0) and in the week immediately post-intervention (T1). Every time to measure data is face-to-face with participants. We expect the intervention to improve the abilities of patients to take care of themselves. Therefore, we choose the activities of daily living measured in the week immediately post-intervention (T1) as the primary outcome. Self-esteem, rehabilitation self-efficacy, positive emotion, upper limb function, and safety will be the secondary outcomes.

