#### Upper limb function

2.6.5

Upper limb function will be measured by the Fugl-Meyer Assessment, which is one of the important scales for evaluating the motor function of stroke patients, with the advantages of reliability and high sensitivity (35). The upper limb dimension of the simplified Fugl-Meyer Assessment has 33 items. Each item is scored from 0 (cannot be completed) to 2 (completed). The total score ranges from 0 to 66. The higher the total score, the better the motor function of the upper limbs and hands.

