#### Activities of daily living

2.6.6

The modified Barthel Index will be used to evaluate the activities of daily living. This scale has 10 items, and each item is divided into 5 levels according to the degree of dependence (36). The total score ranges from 0 to 100. The higher the total score, the better the self-care ability.

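### Eligibility sets no upper limit on the baseline modified Barthel Index, so patients already at 100 can be randomized although they cannot improve on the primary outcome

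*Protocol article*

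**What the plan says.** Section 2.6 names the endpoint: "we choose the activities of daily living measured in the week immediately post-intervention (T1) as the primary outcome". Its stated rationale is "We expect the intervention to improve the abilities of patients to take care of themselves". Section 2.6.6 names the instrument, "The modified Barthel Index will be used to evaluate the activities of daily living", and gives its bounds: "The total score ranges from 0 to 100. The higher the total score, the better the self-care ability".

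Section 2.2 lists eight inclusion and six exclusion criteria. The motor criterion is "with upper limb dysfunction and Brunnstrom stages I to VI", and patients are taken "whether in the acute, subacute, or chronic phase of stroke". One exclusion concerns lesion size: "largest slice diameter of cerebral infarction is greater than 3.0 cm, or the infarction spreads to two brain lobes", or a haematoma above 30 mL. No criterion refers to the Barthel score or requires any loss of self-care.

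On timing, section 2.2 puts eligibility first, then consent and baseline data. Section 2.3 places randomization after the initial evaluation. Section 2.1 sets a floor of 35 per group, with the final number to be calculated from Barthel scores after a 12-patient pilot.

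**The concern.** The trial asks whether self-care improves, and measures it on a scale with a fixed top. Eligibility is set by the arm, not by self-care. Arm dysfunction has no threshold in section 2.2, so it does not guarantee that a patient has points left to gain on the Barthel Index. The severity limits that can be read from the text (lesion size, normal cognition and communication) are aimed at more severe strokes. None is aimed at patients who are already independent.

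Every arm also receives usual rehabilitation before T1, so some patients below 100 at T0 may reach the cap without the experimental therapy. Patients at the cap count toward the sample size but pull the observed difference toward zero. The contrast of music plus robot against robot alone is the more exposed one if the robot itself raises scores, because its comparator then starts closer to the cap. A small or null difference could then partly reflect the limit of the scale.

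**Working it through.** **Step 1: the criteria against the endpoint.**
- Inclusion (1) to (3) fix diagnosis, age and stability, and admit any phase of stroke.
- Inclusion (4) requires arm dysfunction and a Brunnstrom stage.
- Inclusion (5) to (8) concern cognition, senses, music background and consent.
- The exclusions concern organ disease, mental history, local arm problems, large lesions, cooperation and depression.

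A patient with some arm dysfunction and a Barthel score of 100 passes all fourteen. That patient's largest possible gain is 100 − 100 = 0 points. A patient at 95 can gain at most 5.

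**Step 2: inputs for the size.** From the document: cap of 100, two-sided 0.05, at least 35 per group. The document states no effect size, SD, power or baseline distribution, so the floor of 35 cannot be reproduced. Assumed: an SD of 20 before clipping and a true gain of 13.6 points. This gives d = 13.6/20 = 0.68, which has 80% power at 35 per group for one pairwise t-test (noncentral t).

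**Step 3: formula.** Let X be normal with mean μ and SD σ = 20, and let the recorded score be min(X, 100). With k = (100 − μ)/σ:
- share at 100 = 1 − Φ(k)
- mean recorded score = μΦ(k) − σφ(k) + 100(1 − Φ(k))

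Example, control mean 90:
- Control: k = 0.50, and the mean is 90 × 0.6915 − 20 × 0.3521 + 100 × 0.3085 = 86.04.
- Experimental: μ = 103.6, k = −0.18, and the mean is 103.6 × 0.4286 − 20 × 0.3925 + 100 × 0.5714 = 93.69.
- Observable gain: about 7.6 points, a loss of 1 − 7.6/13.6 = 44%.
- The clipped SDs are 14.88 and 10.44, so the pooled SD is √((14.88² + 10.44²)/2) = 12.85 and d is about 0.60.

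**Step 4: results at 35 per group.**

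| Control mean before clipping | Controls at 100 | Experimental arm at 100 | Observable gain | Understated by | Power |
|---|---|---|---|---|---|
| 60 | 2% | 9% | 12.9 | 5% | 80% |
| 70 | 7% | 21% | 11.9 | 13% | 79% |
| 80 | 16% | 37% | 10.1 | 26% | 76% |
| 90 | 31% | 57% | 7.6 | 44% | 69% |

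Power falls less than the gain because the cap also compresses the SD.

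**Step 5: does excluding only T0 = 100 help?** This uses a second model with its own assumptions: baseline mean 80 and SD 20 clipped at 100, usual-care gain 12 (SD 10), true effect 15, and 35 per group. Without exclusion the observable difference is 7.7 points and power is 67%. The share at 100 at T0 is 1 − Φ((100 − 80)/20) = 16%. If those patients showed no difference at all, the rest would show 7.7/0.84 = 9.2 points. Direct simulation of the restricted sample gives 9.0 points and 78% power, because patients at 100 still show a small difference in this model. The exclusion therefore recovers part of the loss but not all of it.

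**The case against.** **Broad eligibility is a legitimate choice, and a cap acts on all arms alike.** This stands in so far as the cap favours no arm. It still shrinks the estimate. The introduction motivates the trial by declining self-care, and a patient at 100 has no such decline on this scale.

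**The setting makes full independence unlikely.** Participants are newly admitted neurology inpatients expected to accept three weeks of rehabilitation, so few may score 100. That may be so, and the loss would then be negligible, as the first row of the table shows. The criteria do not secure it.

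**Thirty-five is a floor, and the pilot will re-size the trial.** Pilot scores would carry any ceiling with them, so a larger sample could restore power. It would not restore the attenuated difference. Twelve patients, about four per arm if allocated 1:1:1, also say little about the upper tail, and no eligibility response to the pilot is described.

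**Stronger readings that a reader might infer, and why they are not supported:**
- That Brunnstrom I to VI excludes nobody. The article never says how many stages the scale has.
- That the arm scale needs the same limit because "The total score ranges from 0 to 66". A patient at 66 would hardly meet the requirement of upper limb dysfunction, so that exclusion would be largely redundant.
- That patients near the top cannot improve. This is strictly true only at 100.
- That power collapses. Treating a share of patients as having zero effect with an unchanged SD gives 71%, 61% or 50% for shares of 10%, 20% or 30%. That ignores the compressed SD. With 31% of controls at the cap it gives 49%, against 69% when the cap itself is modelled.

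**Conclusion.** The gap is certain from the text: section 2.2 allows randomization of patients whose primary outcome cannot improve. Its size is not known, because the article gives no baseline Barthel scores. Under an SD of 20, a true gain of 13.6 points and a control mean of 60 to 90, the estimate is understated by 5% to 44%, and power at the floor of 35 per group lies between 80% and 69%. The power loss is at most about 5 percentage points unless the control mean approaches 90. Attenuation of the estimate is the main harm. The documents do not show that a ceiling will occur, nor that the trial cannot answer its question. The point merits a change because it is cheap and re-sizing cannot repair the estimate.

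**What to change.** Add to section 2.2 that the T0 modified Barthel Index must be below 100, or below a lower cut-off that the sponsor pre-specifies after seeing the pilot scores and before the main trial starts. Apply the rule before randomization. Report the share of each arm scoring 100 at T0 and at T1, so that readers can judge how much the scale limited the result.

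No new assessment is needed, since baseline data are already collected before allocation and eligibility already depends on one rating scale (the depression exclusion). The costs are slightly slower recruitment from the expected 10 patients per month, a few patients who have consented but are not randomized because T0 follows consent, and results that apply to patients with measurable dependence. Requiring only a score below 100 leaves patients just under the cap in the trial, which is the reason to consider a lower cut-off once the pilot scores are known.

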### Randomization

2.3

The random number table was generated based on the RV.Uniform function of SPSS 22.0 software. All participants will be randomly assigned to one of the three groups in a 1:1:1 ratio after initial evaluation. Participants will be randomly allocated via an online service provided by the Innovation Center of Nursing Research at the West China Hospital.

### Blinding

2.4

Blinding of participants is not possible due to the obvious difference in intervention content. Participants of different groups would not live in the same ward, and the intervention would be implemented in a separate room. For practical reasons, researchers cannot be blinded because they need to clearly know the intervention process and content. In addition, follow-up of all participants, management, and other study tasks will be completed by the same researchers. A separation of tasks and blinding will be impossible. However, we will ensure the full concealment of allocation. The randomization of participants was conducted by a non-intervener by using sealed envelopes. Finally, the data collector and study statistician will be blinded to participants’ allocation.

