## Methods

2

This study is a single-blind, three-arm randomized controlled trial with randomization at the participant level. This trial was approved by the Ethics Committee of West China Hospital of Sichuan University (number: 2022–852) and was registered on the Chinese Clinical Trial Registry (number: ChiCTR2200063738). Activities of daily living will be the primary endpoint to examine whether usual rehabilitation treatment and care plus robot-assisted rehabilitation and reminiscent music therapy for older patients with upper limb dysfunction after stroke improve physical and mental health. All outcomes will be collected for three groups at baseline (T0) and in the week immediately post-intervention (T1). The overview of the study design is shown in Figure 1, and this study protocol followed the statement of the Consolidated Standard of Reporting Trials (CONSORT) (28).

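### Keeping the arms in different wards can reveal allocation to the face-to-face T1 assessor, and the blinding section conflicts with itself on whether assessment is separated from unblinded staff

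*Protocol article*

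**What the plan says.** The trial is described in section 2 (Methods) as a "three-arm randomized controlled trial with randomization at the participant level". Section 2.2 (Recruitment) places all recruitment in one setting: "Researchers will recruit participants by approaching potentially eligible participants in the neurology ward". After randomization the arms are kept apart (section 2.4, Blinding): "Participants of different groups would not live in the same ward, and the intervention would be implemented in a separate room".

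Section 2.4 also says that neither participants nor researchers can be blinded, and continues: "follow-up of all participants, management, and other study tasks will be completed by the same researchers. A separation of tasks and blinding will be impossible". It closes in the other direction: "Finally, the data collector and study statistician will be blinded" to allocation.

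Section 2.6 (Outcomes and measurements) gives the measuring to one person: "A research assistant who does not know the randomization scheme will perform the data collection and examinations at baseline (T0"), and likewise at T1. It adds that every measurement is made face to face. Section 2.2, however, has the researchers who recruit and take consent also collect the baseline data.

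**The concern.** Participants and treating researchers know the allocation, so the blinded data collector is the main protection against rating bias. Two features of section 2.4 weaken that protection.

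First, under the separation rule everyone in a given ward or room is in the same arm. An assessor who knows where a patient stays may be able to work out the group. One patient who mentions the treatment can also unmask the others housed there. Not knowing the randomization scheme does not prevent either route. The primary outcome grades each item by degree of dependence (section 2.6.6), and the Fugl-Meyer items are scored 0 to 2 (section 2.6.5). Both leave room for judgement. In addition, doctors and specialized nurses shape and deliver usual care in all three arms (section 2.5.1). If that care differs between locations, the difference is carried into the arm comparison.

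Second, a reader cannot tell from section 2.4 whether outcome assessment is one of the tasks that the unblinded researchers perform.

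**Working it through.** **The text, side by side**

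1. *Location and arm.* Section 2 randomizes individuals; section 2.4 then allows no ward to contain two arms. Ward is therefore nested in arm, whatever the number of wards.
2. *What is exposed.* Sections 2.3 and 2.5 randomize after the initial evaluation. Placement by arm can therefore unmask T1 but not T0. T1 is the only post-baseline assessment and carries the primary outcome.
3. *Who does what.* Section 2.4 gives follow-up and other study tasks to unblinded researchers and rules out separating tasks. The end of section 2.4 and section 2.6 require a blinded collector who is separate from them. Taken literally these conflict. They agree only if the statement on impossibility excludes outcome assessment, which the text does not say.
4. *Baseline.* Section 2.2 gives T0 collection to the researchers; section 2.6 gives it to the research assistant.
5. *Analysis.* Section 2.7.1 names analysis of variance or the Kruskal–Wallis test between groups, with no term for ward.

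**Illustration of size**

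The protocol article gives no figure to reproduce.

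Inputs from the document: at least 35 per group (section 2.1); two-sided tests at 0.05 (section 2.7.1). Assumed: the intraclass correlation (ICC) of outcomes within a location, the number of locations per arm, and any rating shift.

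*Clustering by location.* For m patients per location, the design effect is DE = 1 + (m − 1) × ICC. The true two-sided type I error of a pairwise z-test that ignores location is 2 × [1 − Φ(1.96/√DE)].

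| ICC | One ward per arm (m = 35): DE | Type I error | Five rooms per arm (m = 7): DE | Type I error |
|---|---|---|---|---|
| 0.01 | 1 + 34 × 0.01 = 1.34 | 0.090 | 1 + 6 × 0.01 = 1.06 | 0.057 |
| 0.02 | 1 + 34 × 0.02 = 1.68 | 0.130 | 1 + 6 × 0.02 = 1.12 | 0.064 |
| 0.05 | 1 + 34 × 0.05 = 2.70 | 0.233 | 1 + 6 × 0.05 = 1.30 | 0.086 |

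*Systematic shift.* Suppose unmasked rating, or a difference in care, moves one arm by b standard deviations when there is no true effect. With s = b/√(2/35), the type I error is 1 − Φ(1.96 − s) + Φ(−1.96 − s). For b = 0.1, 0.2, 0.3 and 0.4 this gives 0.070, 0.133, 0.241 and 0.387. For example, b = 0.2 gives s = 0.2/0.239 = 0.837.

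**The case against.** The best defence has four parts.

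- *Ward may mean room.* Recruitment is from a single neurology ward, so the separation may be between rooms within it. The same staff could then serve all arms, and rooms could change arm as patients come and go. This stands. A reader might infer that ward care is fully confounded with treatment and that no analysis could separate them. That holds only with one fixed ward per arm, which the document does not state. The larger error rates depend on the same assumption.
- *The place of T1 is not given.* Section 2.1 expects stays of up to 20 days against three weeks (21 days) of training, and T1 falls in the week after training, so some assessments may follow discharge. This also stands: location can reveal the arm, but the text does not show that it will.
- *Two roles can coexist.* Unblinded researchers and a separate blinded assistant are compatible. A reader might infer that the two statements in section 2.4 cannot both be true. That goes too far, because a narrower reading of the statement on impossibility reconciles them. As printed, though, that statement is unrestricted, and section 2.2 adds a further mismatch on who collects T0.
- *Separation limits contamination.* This is a legitimate aim in a trial without participant blinding. The treatment is, however, already given in a separate room (section 2.4) and the music through a headset (section 2.5.3), so the added protection may be modest. The document does not measure it, and shared wards could let patients talk about the intervention.

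**Conclusion.** The point holds in conditional form. The separation rule makes location a possible marker of arm for the T1 assessor, and it mixes any difference in care between locations with the arm effect. Section 2.4 also conflicts, as worded, with its own promise of a blinded data collector and with section 2.6. Section 2.2 conflicts with section 2.6 on who collects T0.

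The size is unknown. The clustering figures run from about 6% to 23% over the assumed ICCs and the two layouts, and none of them contradicts a number in the document. A rating shift of 0.2 standard deviations, also assumed, would by itself take the error to about 13%. The case for changing the text rests on the exposure of the primary outcome to rating bias and on the conflicting statements, and it does not need any particular ICC.

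**What to change.** 1. Have the modified Barthel Index and Fugl-Meyer at T1 rated in one common place away from the wards, by the research assistant already planned. State that this person has no treatment, follow-up or ward-list role, and ask participants not to mention their group.
2. Restrict "A separation of tasks and blinding will be impossible" to treatment delivery and general management, so that it does not cover outcome assessment.
3. Reconcile sections 2.2 and 2.6 on who collects T0. Its timing before allocation is already planned and needs no change.
4. Say whether ward means a ward or a room. Where feasible, do not fix a location to an arm; otherwise report the tie as a limitation.

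Items 2 and 3 are wording only. Item 1 needs a room and some scheduling but no new staff. Item 4 may cost some contamination if arms share a location, so the sponsor should weigh it; items 1 to 3 do not depend on that choice.

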### Interventions

2.5

All participants will be randomly assigned to receive usual rehabilitation treatment and care (control), usual rehabilitation treatment and care plus robot-assisted rehabilitation and reminiscent music therapy (experimental group 1), or usual rehabilitation treatment and care plus robot-assisted rehabilitation (experimental group 2) in a 1:1:1 ratio after initial evaluation.

#### Usual rehabilitation treatment and care

2.5.1

Usual rehabilitation treatment mainly includes drug treatment, comprehensive training of hemiplegic limbs, physical therapy, and so on, which will be formulated and implemented by rehabilitation doctors and neurologists according to the specific conditions of the participants. Usual rehabilitation care includes basic environmental care, diet care, drug care, health education, psychological care, and rehabilitation care, which will be formulated and implemented by specialized nurses according to the specific conditions of the participants.

#### Robot-assisted rehabilitation

2.5.2

According to the specific conditions of the patients, the rehabilitation doctors will use the rehabilitation robot for the upper limb to carry out 40 min of rehabilitation training for the patients, five times per week for 3 weeks. The individualized rehabilitation scheme will be formulated by rehabilitation doctors and neurologists according to the specific situation of the patients. The robot equipment used in this study is a three-dimensional upper limb rehabilitation robot (model: A6) produced by Guangzhou Yikang Medical Equipment Industry Co., Ltd. Rehabilitation doctors need to undergo strict training from the manufacturer before they can operate the equipment. This robot equipment has five training modes: passive mode, active-passive mode, active mode, prescription mode, and track editing mode.

#### Reminiscent music therapy

2.5.3

The same research group developed a music library of reminiscent songs in the early stage, including 100 Chinese songs released from 1935 to 1980, which are divided into 10 song lists and each list has 10 reminiscent songs. Each time the robot-assisted rehabilitation training of the upper limb is carried out, a reminiscent song list will be played for patients with a wireless headset. When playing music, the music beat and intensity will be between 45 and 60 decibels. After the robot-assisted rehabilitation training of the upper limb, the patients will be asked to sit down in a comfortable position and concentrate on breathing for 2 min. Patients should first slowly inhale for 3 s, pause for 1 s, then slowly exhale for 5 s, exhale all the residual gas in the lungs and imagine that the annoyance and unhappiness could be dissipated with the exhalation of the gas. The whole process of breathing relaxation is slow and uniform with rhythm, with a total of 5 cycles.

